## Abstract

**Background:**

Colorectal cancer (CRC) is one of the most commonly occurring neoplasms and a leading cause of cancer death worldwide, and new preventive strategies are needed to lower the burden of this disease. Eicosapentaenoic acid (EPA), the omega-3 polyunsaturated fatty acid that is widely used in the treatment of hyperlipidemia and prevention of cardiovascular disease, has recently been suggested to have a suppressive effect on tumorigenesis and cancer cell growth. In CRC chemoprevention trials, in general, the incidence of polyps or of the cancer itself is set as the study endpoint. Although the incidence rate of CRC would be the most reliable endpoint, use of this endpoint would be unsuitable for chemoprevention trials, because of the relatively low occurrence rate of CRC in the general population and the long-term observation period that it would necessitate. Moreover, there is an ethical problem in conducting long-term trials to determine whether a test drug might be effective or harmful. Aberrant crypt foci (ACF), defined as lesions containing crypts that are larger in diameter and stain more darkly with methylene blue than normal crypts, are considered as a reliable surrogate biomarker of CRC. Thus, we devised a prospective randomized controlled trial as a preliminary study prior to a CRC chemoprevention trial to evaluate the chemopreventive effect of EPA against colorectal ACF formation and the safety of this drug, in patients scheduled for polypectomy.

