### Sample size estimation

In the chemoprevention trial conducted in FAP patients, the NSAID sulindac and selective cyclooxygenase-2 (COX-2) inhibitor celecoxib reduced polyposis of the retained rectum after colectomy with ileorectal anastamosis (IRA). As previously noted, EPA has a suppressive effect for polyp formation and proliferation of FAP [19]. From these reports, we estimated that NSAIDs and EPA may have equivalent effect on suppression of polyp formation and proliferation.

Based on the target in the NSAIDs chemoprevention study for ACF, Takayama et al. reported that sulindac administration at 300 mg/d for 2 months to post-polypectomy patients suppressed ACF formation, decreasing the number of ACF from 7.70 ± 4.04 (baseline) to 4.00 ± 2.95 (at 2 months, *p < 0.001*) [33]. Presuming EPA and sulindac may have equivalent effect in suppressing ACF formation, to detect the reduction in the number of ACFs in the EPA group using the Mann–Whitney U test with a two-sided significance level of 5% and a power of 80%, it was estimated that a sample size of 12 patients per group would be necessary. Assuming a 10% dropout rate, we propose to recruit 15 patients per group, that is, a total of 30 patients.

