### Statistical analysis

The number of ACFs in each group, the primary endpoint, will be compared between the EPA group and the placebo group by the Mann–Whitney U test. The safety, one of the secondary endpoints, will be compared by the chi-square test. The remaining results in the two groups will be compared by the Mann–Whitney U test or Student’s *t* test. A P values of < 0.05 will be regarded as indicative of significance. The analysis will be performed using SPSS, version 17.0 (SPSS Inc., Chicago, Il.).

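### The stated safety aim is served only by a chi-square test at P < 0.05 with 15 patients per arm, which cannot bound the excess adverse event risk; a risk difference with its confidence interval can

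*Protocol article*

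**What the plan says.** The Background of the abstract gives the purpose of the trial as "to evaluate the chemopreventive effect of EPA against colorectal ACF formation and the safety of this drug". Under Outcome measurements, drug safety is the first of the secondary outcomes: adverse events are graded by NCI-CTCAE version 4.0 and recorded in a patient diary. Laboratory data are a separate outcome, the fourth in that list.

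The Statistical analysis section fixes the comparison: "The safety, one of the secondary endpoints, will be compared by the chi-square test". The threshold follows in the same section: "A P values of < 0.05 will be regarded as indicative of significance".

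Sample size estimation rests on ACF counts only: "it was estimated that a sample size of 12 patients per group would be necessary". Allowing for dropout, "we propose to recruit 15 patients per group, that is, a total of 30 patients". It states no adverse event rate, no difference to be detected and no power for safety.

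**The concern.** A test of no difference can flag harm when the P value is small. When it is not small, the test says nothing about how large an excess risk remains compatible with the data, and that is the question a safety aim asks. With 15 patients per arm, a non-significant result is likely under several sizeable increases in adverse events, so it carries little information.

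The abstract and the Discussion present this trial as the step before a longer chemoprevention trial. If its safety result is reported only as a P value, a finding of no significant difference could feed that decision while large excess risks remain open.

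**Working it through.** **Inputs from the article.** 15 patients per arm (Sample size estimation); chi-square test, threshold 0.05 (Statistical analysis). A chi-square test on a 2x2 table is two-sided.

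**Inputs that are assumptions.** The article gives no adverse event rates, so every pair of rates below is assumed. I take the chi-square test without continuity correction and all 15 patients per arm as analysed, which is the case most favourable to the plan.

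**The plan's own figure.** 12 evaluable per arm with 10% dropout gives 12 / (1 - 0.10) = 13.3, so 14; the plan recruits 15. This is within one patient. There is no stated power for safety to reproduce.

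**Miss rate of the test.** With a events among n placebo patients and b among n EPA patients,

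X² = 2n [a(n - b) - b(n - a)]² / [n² (a + b)(2n - a - b)], significant if P < 0.05 on 1 degree of freedom.

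Power is the sum, over all tables with P < 0.05, of Bin(a; n, p_placebo) × Bin(b; n, p_EPA). The miss rate is 1 - power. With n = 15:

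| Placebo vs EPA (assumed) | Power | Missed |
|---|---|---|
| 5% vs 15% | 0.089 | 91% |
| 10% vs 30% | 0.278 | 72% |
| 15% vs 45% | 0.461 | 54% |
| 20% vs 60% | 0.627 | 37% |
| 25% vs 75% | 0.808 | 19% |

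All five rows are threefold rises, so the ratio alone does not fix the miss rate; the placebo rate does. A doubling from 10% to 20% is missed 90% of the time (power 0.101). From a 10% placebo rate, 80% power is reached only at about 55% on EPA (power 0.810).

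For 10% vs 30%, less favourable conditions give higher miss rates: 80% with 12 per arm (power 0.198), 85% with Fisher's test and 15 per arm (power 0.149), and 89% with Yates' correction and 15 per arm (power 0.107).

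**An illustration that needs no assumed rate.** Suppose 3 of 15 EPA patients and 0 of 15 placebo patients have an event.

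- X² = 30 × (3 × 15 - 0 × 12)² / (15 × 15 × 3 × 27) = 60,750 / 18,225 = 3.33, so P = 0.068, not significant under the plan.
- Wilson 95% limits: 3/15 gives 0.070 to 0.452; 0/15 gives 0 to 0.204.
- Newcombe lower limit: 0.20 - √[(0.20 - 0.070)² + (0.204 - 0)²] = 0.20 - 0.24 = -0.04.
- Newcombe upper limit: 0.20 + √[(0.452 - 0.20)² + (0 - 0)²] = 0.45.

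The plan would report this as no significant difference. The interval shows that an excess of up to 45 percentage points is not ruled out.

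**No events at all.** With 0/15 in both arms the Newcombe interval is -20 to +20 points. The exact two-sided 95% upper bound for one arm is 1 - 0.025^(1/15) = 0.218, or about 22%.

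**The case against.** **The article does not draw the faulty inference.** A reader might infer that the protocol will declare EPA safe if P exceeds 0.05. The text does not support that. It says that the arms will be compared and that a small P value indicates significance; it sets no go/no-go rule on safety. This stands, and the point is therefore not that the plan contains an error or a contradiction.

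**72% is not a property of the design.** A reader might also take it that the test misses any threefold rise 72% of the time. That figure belongs to an assumed 10% vs 30%. The range in the table must go with it, and at high event rates the test performs tolerably.

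**Safety does not rest on this test alone.** The plan has a diary, CTCAE grading, a withdrawal rule for grade 3 or worse events and a Data Monitoring Committee. It also cites prior evidence that EPA is well tolerated. The aim at the end of the main Background section names only the ACF effect. This limits the weight of the point. But the withdrawal rule and the committee protect individuals and oversee conduct, and neither compares the arms.

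**Low power for safety is normal in a 30-patient preliminary trial, and reporting detail belongs in an analysis plan that is not shown.** The first part is true, and is itself the reason to estimate rather than test. The second would decide the matter if the article were silent. It is not silent: it names a specific method for safety, and that method does not fit the aim.

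**Laboratory values.** One might extend the point to creatinine or urea nitrogen. The article lists laboratory data as a separate outcome with its own tests, so the point is confined to adverse events.

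**Conclusion.** The point holds as a cheap improvement. The abstract names safety as an aim, and the one between-arm analysis stated for it cannot bound the excess adverse event risk. Under assumed rates, with 15 per arm analysed and no continuity correction, threefold rises are missed from 91% down to 19% of the time as the placebo rate goes from 5% to 25%, with 72% at 10% vs 30%. The 3/15 vs 0/15 illustration rests on no assumed rate and shows the same thing. The primary endpoint, the allocation and the sample size are unaffected.

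**What to change.** In Statistical analysis, replace the safety sentence with wording such as:

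*Safety will be reported as the number and proportion of patients with any adverse event, and with adverse events by CTCAE grade, in each group. The risk difference (EPA minus placebo) will be given with its 95% confidence interval (Newcombe or exact), and with an exact upper bound where no event is seen. Any P value is supplementary, and a non-significant result will not be taken as evidence of safety.*

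The authors should choose the interval method before unblinding.

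The cost is two or three sentences. The intervals come from data already to be collected, and no patients, visits or clinical rules change. The downside is that the intervals will be wide, so the safety statement will read less favourably than a bare non-significant P value.

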### Trial Steering Committee and Data Monitoring Committee

The Trial Steering Committee and Data Monitoring Committee shall be located at the Department of Gastroenterology, Kanto Medical Center, NTT East. The committee shall consist of three people: [name]., [name]., and [name]. The Management Team will monitor the trial progress status and data by face-to-face and/or telephonic contact with each of the sites every month.

### Study flow

A flow chart of the study is shown in Figure 1.

**Figure 1 F1:**
[figure not shown]
Study Flow.

## Discussion

This is the first study proposed to explore the effect of EPA against colorectal ACF formation. Knowledge of the mechanisms underlying the anti-neoplastic activity of EPA remains nebulous. Current understanding of the mechanistic aspects of the anticancer activity of EPA has been reviewed in detail in published reviews [38-41]. In general, the major mechanisms proposed to underlie the anti-neoplastic activities of EPA; (1) modulation of COX activity, (2) alteration of the membrane dynamics and cell surface receptor function, and (3) increased cellular oxidative stress. However, the in vivo relevance of each of the above putative mechanisms and their relative contributions to the anticancer activity of EPA remain unclear. Several in-vitro studies have explored the anti-neoplastic activity of omega-3 PUFAs against human CRC cells, and EPA treatment has been shown to reduce cellular proliferative activity and increase cellular apoptotic activity [42-45]. EPA can act as an alternative substrate for COX-2, instead of AA, leading to a reduction in the formation of the pro-tumorigenic ‘2-series’ PGs (e.g., PGE_2_) in favor of the ‘three-series’ PGs (e.g., PGE_3_) in several cell types, including CRC cells [46-48]. Furthermore, incorporation of EPA into the cell phospholipid membrane alters the fluidity, structure, and/or function of the lipid rafts or calveolae [49], which are sphingolipid- and cholesterol-rich microdomains that float freely in the cell membrane. The localization of cell surface receptors, such as epidermal growth factor receptor (EGFR) [50], in lipid rafts is believed to be crucial for downstream receptor signaling, controlling proliferation and apoptosis [51,52]. Furthermore, EPA may exert an antineoplastic effect through alteration of the cellular redox state and of the oxidative stress exposure of the cells. PUFAs are highly peroxidizable, which generates reactive oxygen species (ROS), such as superoxide radicals. Many tumor cells display altered cellular pathways for the handling of ROS, including depletion of the major intracellular antioxidant, glutathione. Subsequent elevation of the intracellular ROS levels by EPA has been hypothesized to induce cancer cell apoptosis [53].

This trial may have the following limitations. First, ACF are considered as a reliable surrogate biomarker of CRC, [21] although their biological significance still remains controversial. In CRC chemoprevention trials, in general, the incidence of polyps or of the cancer itself is set as the study endpoint. Although the incidence rate of CRC would be the most reliable endpoint, use of this endpoint would be unsuitable for chemoprevention trials, because of the relatively low occurrence rate of CRC in the general population [18] and the long-term observation period that it would necessitate. We previously reported the usefulness of ACF as a biological marker of CRC [26,27] and carried out a chemoprevention trial for colorectal ACF [28,29]. Thus, we devised a trial using this endpoint (ACF) to evaluate the chemopreventive effect of EPA. Second, we do not propose to conduct a dose–response study in respect of the effect of EPA on ACF formation. Until now, trials of EPA for cancer prevention and adjuvant treatment have been conducted using EPA at doses of 1000 – 4000 mg per day. In Japan, the EPA drug product specification is 0.9 g, and 2.7 g of EPA has been commonly used and very well tolerated. Therefore, we planned to conduct this trial using 2.7 g of EPA per day. Third, an intervention period of 1 month may be too short to allow reliable detection of differences between the groups. However, we showed in a previous study that oral administration of metformin for 1 month suppressed the formation of colorectal ACF in humans [29]. If the intervention agents had a chemopreventive effect, an intervention period of 1 month would be sufficient to evaluate the changes in the number of ACF.

We previously conducted a short-term chemoprevention trial of metformin for colorectal ACF, and showed the suppressive effect of the drug on the formation of ACF. Thereafter, we are conducting a long-term metformin chemoprevention trial for colorectal polyps, the trial registered in the UMIN Clinical Trials Registry as UMIN000006254 [34]. We propose to repeat the same step for the chemoprevention trial using EPA.

If EPA were found to be effective for the prevention of CRC, the impact would be extremely large. We consider it of interest, therefore, to determine whether EPA might suppress the formation of human colorectal ACFs.

## Abbreviations

CRC: Colorectal cancer; NSAIDs: Nonsteroidal anti-inflammatory drugs; COX-2: Cyclooxygenase-2; ACF: Aberrant crypt foci; EPA: Eicosapentaenoic acid; PUFA: Polyunsaturated fatty acid; AA: Arachidonic acid; PG: Prostaglandin; FAP: Familial adenomatous polyposis; FFA: Free fatty acid (FFA); DHA: Docosahexaenoic acid; PCNA: Proliferative cell nuclear antigen; TUNEL: Terminal deoxynucleotidyl transferase-mediated dUTP-biotin nick-end labeling.

## Current study status

This trial began recruiting patients in June 2012 and shall complete recruitment in December 2012. Data collection is due to be completed in March 2013, and the results are scheduled to be published in June 2013.
